# Tocolysis in the management of preterm prelabor rupture of membranes at 22–33 weeks of gestation: study protocol for a multicenter, double-blind, randomized controlled trial comparing nifedipine with placebo (TOCOPROM)

**DOI:** 10.1186/s12884-021-04047-2

**Published:** 2021-09-08

**Keywords:** Tocolysis, Nifedipine, Randomized controlled trial, Pregnancy, Preterm birth, Preterm prelabor rupture of membranes, Neonatal outcome

## Abstract

**Background:**

Preterm prelabor rupture of membranes (PPROM) before 34 weeks of gestation complicates 1% of pregnancies and accounts for one-third of preterm births. International guidelines recommend expectant management, along with antenatal steroids before 34 weeks and antibiotics. Up-to-date evidence about the risks and benefits of administering tocolysis after PPROM, however, is lacking. In theory, reducing uterine contractility could delay delivery and reduce the risks of prematurity and its adverse short- and long-term consequences, but it might also prolong fetal exposure to inflammation, infection, and acute obstetric complications, potentially associated with neonatal death or long-term sequelae. The primary objective of this study is to assess whether short-term (48 h) tocolysis reduces perinatal mortality/morbidity in PPROM at 22 to 33 completed weeks of gestation.

**Methods:**

A randomized, double-blind, placebo-controlled, superiority trial will be performed in 29 French maternity units. Women with PPROM between 22^0/7^ and 33^6/7^ weeks of gestation, a singleton pregnancy, and no condition contraindicating expectant management will be randomized to receive a 48-hour oral treatment by either nifedipine or placebo (1:1 ratio). The primary outcome will be the occurrence of perinatal mortality/morbidity, a composite outcome including fetal death, neonatal death, or severe neonatal morbidity before discharge. If we assume an alpha-risk of 0.05 and beta-risk of 0.20 (i.e., a statistical power of 80%), 702 women (351 per arm) are required to show a reduction of the primary endpoint from 35% (placebo group) to 25% (nifedipine group). We plan to increase the required number of subjects by 20%, to replace any patients who leave the study early. The total number of subjects required is thus 850. Data will be analyzed by the intention-to-treat principle.

**Discussion:**

This trial will inform practices and policies worldwide. Optimized prenatal management to improve the prognosis of infants born preterm could benefit about 50,000 women in the European Union and 40,000 in the United States each year.

**Trial registration:**

ClinicalTrials.gov identifier: NCT03976063 (registration date June 5, 2019).

**Supplementary Information:**

The online version contains supplementary material available at 10.1186/s12884-021-04047-2.

## Background

### Rationale

#### Epidemiology of PPROM and neonatal consequences

Preterm prelabor rupture of membranes (PPROM) is defined as spontaneous rupture of the fetal membranes occurring before the onset of labor and before 37 weeks of gestation [1, 2]. PPROM is a complex and multifactorial pathology, resulting from the progressive weakening of the membranes under the effect of chemical, mechanical, and/or infectious factors [3]. This degeneration begins several weeks before manifesting clinically by the flow of amniotic fluid [4, 5]. Primary and secondary prevention of preterm birth are very challenging: although some risk factors have been identified, most women have none, and there are no validated predictive models and no effective preventive interventions [6, 7].

PPROM complicates 2–3% of pregnancies [1, 7]. Despite the rupture of membranes, pregnancy can be prolonged by a latency period (defined as the time elapsed from PPROM to delivery) ranging from a few hours to several weeks. About 50 to 60% of women will give birth within the first week after PPROM [8–10], which is thus responsible for a large share of preterm births (25 to 30%) [1, 11] and is a leading cause of neonatal mortality and morbidity and maternal infectious morbidity [7, 12]. Although the infant’s prognosis depends mainly on gestational age at birth [13–15], fetal exposure to inflammation, infection, and acute obstetric complications (placental abruption, umbilical cord compression or prolapse) can increase short- and long-term mortality/morbidity [16–18]. Consequently, in cases of PPROM, medical teams must weigh the benefits of prolonging pregnancy to reduce prematurity-related adverse consequences against those of inducing delivery to shorten exposure to intrauterine inflammation, infection, and acute obstetric complications.

#### Initial antenatal management

Antenatal management of women follows tertiary prevention principles and aims to reduce maternal, fetal, and neonatal adverse consequences [19]. With PPROM before 34 weeks, current evidence-based care includes expectant management in the absence of labor, overt infection, or fetal distress [20–23] to increase gestational age at birth — the main determinant of the preterm child’s prognosis [13–15]. Routine administration of antibiotics is recommended to prolong pregnancy and reduce neonatal and maternal morbidity [24–27]. The administration of a single course of antenatal steroids is also part of routine care to reduce neonatal mortality, respiratory distress, necrotizing enterocolitis, and intraventricular hemorrhage [28]. Transfer to a tertiary care center should also be offered if necessary [23].

#### A controversial treatment: tocolysis

Tocolysis aims to inhibit uterine contractions and thereby prolong pregnancy at least long enough for a complete course of antenatal steroids and to reduce the consequences of prematurity. However, it can also increase fetal exposure to infection and acute complications.

Only a few randomized controlled trials have addressed the benefits and harms of tocolysis in women with PPROM (Table 1) [29–37]. Overall, they did not demonstrate improvement in neonatal outcomes, and the results regarding the prolongation of gestation remain controversial (Table 1). Most of these trials took place in the 1980s, when steroids and antibiotics were not part of routine care, and performance and reporting biases were not uncommon [12, 38]. Because they were mostly powered to show a difference in latency duration and thus had small sample sizes (6 to 81 patients), their external validity and reliability are limited.

**Table 1 Tab1:** Characteristics of randomized trials comparing initial tocolysis vs. no tocolysis or placebo in women with PPROM

Author, year (reference)	Methods, n	Inclusion criteria	Intervention	Antibiotics / Steroids	Primary outcome	Main result
Christensen, 1980 [29]	RCT, *n* = 30	Singletons, 28–36 wks, with contractions	Ritodrine vs placebo, until 35 wks	Only for urogenital colonization / not specified	Not pre-specified	Significant reduction of deliveries within 24 h, no difference at 48 h
Levy, 1985 [30]	RCT, *n* = 42	Singletons, 25–34 wks, no contractions	Ritodrine vs placebo, until labor	Only if cesarean section / no	Latency period	Significant prolonged mean latency period for treated women
Dunlop, 1986 [31]	RCT, *n* = 48	Singletons, 26–34 wks, no uterine contractions	A: no ritodrine, no cephalexin B: ritodrine, cephalexin C: ritodrine, no cephalexin D: no ritodrine, cephalexin	Only for groups B and D / systematic	Type of labor, mode of delivery, neonatal and maternal outcomes including admission to birth interval	No advantage to the newborn
Garite, 1987 [32]	RCT, *n* = 79	Singletons, 25–30 wks, with or without contractions	Ritodrine vs placebo, until 31 wks	Only if cesarean section / no	Time interval from PPROM to birth	No difference
Weiner, 1988 [33]	RT, *n* = 75 (+ 34 excluded from analyses)	Singletons, up to 34 wks, with contractions	Ritodrine, terbutaline or magnesium sulfate vs bedrest, no clear duration	Only for urogenital colonization / no	Not clearly stated	No difference
Matsuda, 1993 [34]	RT, *n* = 81	Singletons, 23–34 wks, no contractions	Ritodrine vs bedrest, no clear duration	Only for treated women / not specified	Prolongation of pregnancy	Prolongation for more than 72 h was greater for treated women
How, 1998 [35]	RCT, *n* = 145	Singletons and twins, 24–34 wks, not in labor	Magnesium sulfate (treatment initiated only if contractions occurred) vs no tocolysis	Systematic / systematic (weekly)	Not clearly stated	No difference in latency duration, no difference in neonatal outcomes
Ehsanipoor, 2011 [36]	RCT, *n* = 47	Singletons, 24–31 w, no contractions	Indomethacin vs placebo, for 48 h	Systematic / systematic	Delivery within 48 h	No difference
Nijman, 2016 [37]	RCT, *n* = 50	Singletons and twins, 24–33 wks, no contractions	Nifedipine vs placebo, until the onset of labor (up to 18 days or 34 wks)	According to local guidelines / Systematic	Composite of poor neonatal outcome	No difference

*h* hours, *RCT* randomized controlled trial, *RT* randomized trial, *wks* weeks

A systematic review including 8 trials and 408 women compared the potential benefits and harms of any tocolytic therapy with no tocolytic, placebo, or another tocolytic [12]. It found that tocolysis was associated with a significant prolongation of gestation (mean difference 73 h; 95% confidence interval [CI] 20–126; three trials of 198 women) and fewer births within 48 h. Neonatal morbidity (5-min Apgar < 7 and greater need for ventilation) increased as did maternal chorioamnionitis, with no benefits to the infant. The authors concluded that further evaluation of tocolysis is required in women with PPROM treated according to current standards of care.

Two recent studies investigated the association of tocolysis with neonatal outcomes and latency duration based on observational population-based cohort data; they used various approaches to minimize indication bias [38, 39]. Both suggested that tocolysis in PPROM was not associated with improved obstetric, neonatal, or two-year outcomes of preterm infants. Nonetheless, as most clinical guidelines acknowledge, current data are insufficient to support or refute initial tocolysis in women with PPROM [21, 22]. Clinical practices therefore vary widely [40–43].

#### The choice of nifedipine

Several tocolytics have been tested to stop contractions in preterm labor (PTL). In this setting, betamimetics and calcium channel blockers (CCBs) have demonstrated a benefit over placebo in prolonging pregnancy [44, 45], while oxytocin receptor antagonists have not been shown to be superior to placebo, betamimetics, or CCBs (principally nifedipine) for either pregnancy prolongation or neonatal outcomes [46].

For the TOCOPROM trial, we have chosen to use nifedipine, a CCB with a nonspecific relaxant effect on smooth muscles. Although it has rarely been studied for PPROM, nifedipine is commonly recommended and used in France and worldwide for first-line tocolysis to treat spontaneous PTL [47, 48]. Its additional advantages include its favorable safety profile, with severe maternal adverse effects reported only rarely (contrary to betamimetics), and no described fetal or infant complications, as well as oral administration and a reasonable cost (compared with atosiban) [45]. Finally, given its lack of marketing authorization for the treatment of PTL or PPROM, the Pharmacovigilance Technical Committee of the French National Agency of Drug Safety (ANSM) delivered a temporary use recommendation in 2015.

#### Trial aims

The primary objective is to prospectively assess if short-term (48 h) tocolysis reduces perinatal mortality/morbidity in women with PPROM at 22 to 33 completed weeks of gestation by performing a multicenter, randomized, double-blind, placebo-controlled trial.

Its secondary objectives are to assess the impact of tocolysis on prolongation of gestation, maternal morbidity, neonatal morbidity, and outcomes at 2 years of corrected age in cases of PPROM at 22 to 33 weeks.

## Methods and design

### Study design

The TOCOPROM study will be a double-blind, randomized, controlled, superiority, phase III trial comparing two parallel groups receiving a 48-h oral treatment by either nifedipine or placebo (1:1 ratio). The trial protocol (current version 5.0, April 2021) follows the framework of the clinical research and innovation department (Délégation à la Recherche Clinique et à l’Innovation, DRCI, Assistance Publique – Hôpitaux de Paris), which adheres to the Standard Protocol Items: Recommendations for Interventional Trials (SPIRIT) 2013 Statement for protocols of clinical trials [49].

### Setting

This nationwide multicenter trial involves 29 departments of obstetrics and gynecology in France: 24 level III and 5 level II maternity units (Supplementary Table 1).

### Inclusion criteria

Pregnant women are eligible for the trial if they meet all of the following criteria:
PPROM, diagnosed by obstetric teams, between 22^0/7^ and 33^6/7^ weeks of gestation, dated according to the first-trimester ultrasonography.Singleton pregnancy.Fetus alive at randomization.Age ≥ 18 years.Speaks French.Affiliated with the French national health insurance or an equivalent system.Provided written informed consent.

### Exclusion criteria

Pregnant women are not eligible for the trial if they meet any of the following criteria:
PPROM diagnosis ≥24 h after amniotic fluid leak.Ongoing tocolytic treatment at the time of PPROM.Tocolytic treatment with nifedipine between PPROM diagnosis and randomization (*before July 16, 2021, this criterion was “Any tocolytic treatment between PPROM diagnosis and randomization”. This modification was introduced after randomizing 211 patients and was intended to improve the potential for inclusion by making patients receiving a brief tocolysis during* in utero *transfer eligible.)*Fetal condition contraindicating expectant management (including intrauterine infection, placental abruption, hemorrhagic placenta previa, intrauterine fetal demise, non-reassuring fetal heart rate).Cervical dilation ≥5 cm.Iatrogenic rupture of membranes caused by amniocentesis or trophoblast biopsy.Major fetal anomaly.Maternal allergy or contraindication to nifedipine or placebo drug components (myocardial infarction, unstable angina pectoris, hepatic insufficiency, cardiovascular shock, beta blockers, and cardiopathy).Co-administration of diltiazem, rifampicin, transdermal nitrates, or any antihypertensive medication.Hypotension (systolic blood pressure < 90 mmHg).Participation in another interventional research study (Category 1).

### Study intervention

The intervention will be the oral administration of either nifedipine 20 mg or placebo of nifedipine 20 mg (according to the randomization group) for 48 h according to the following administration protocol:
Loading dose: 1 tablet at Time 0 (T0) and T0.5 (i.e., 30 min after the first intake),Maintenance dose: 1 tablet at T3, T11, T19, T27, T35, and T43.

The total treatment duration will be 48 h, with nifedipine total doses of 100 mg on day 1 and 60 mg on day 2.

### Study procedures

#### Recruitment

Each woman presenting at a participating center with possible PPROM will be examined by a midwife or an obstetrician to confirm or rule out this diagnosis. PPROM diagnosis, according to national clinical guidelines, is usually based on 2 positive criteria from maternal history, sterile speculum examination to confirm fluid leakage from the cervical canal, and performance of a diagnostic test [21]. Women transferred from another center will be eligible if PPROM occurred within the previous 24 h and if they did not receive nifedipine after the PPROM diagnosis (women who received other tocolytics during in utero transfer, such as atosiban, which has a very short half-life, are eligible from July 16, 2021 onwards).

Eligible women who meet inclusion criteria will be identified by a local investigator (obstetrician or midwife) and informed about the trial (orally and with a written patient information form) (Table 2). Those who choose to participate, after a reflection period if necessary, will provide written informed consent. A second informed consent form, signed by the mother and father (at inclusion, delivery, or follow-up assessment), is required for the follow-up of children at 2 years of corrected age.

**Table 2 Tab2:**
[figure not shown]
Schedule of enrollment, intervention, and assessment in the TOCOPROM trial

***** A follow-up evaluation at the age of 5 years is under consideration, if additional funding can be obtained

#### Allocation of treatment

After the local investigator (an obstetrician or a midwife) has obtained maternal consent and immediately after inclusion in the trial, he or she will use a centralized procedure provided by a web-based computerized program with secure access (CleanWEB™ software) to randomize the patient. The randomization procedure will use minimization, a dynamic method that allocates subjects to the treatment group that best maintains balance in stratifying factors [49, 50]. Thus, the randomization list is not produced before the trial starts, but during participant recruitment. Minimization will be based on three prognostic factors: uterine contractions felt by the patient at the time of inclusion (presence or absence), recruiting center (1 to 29), and gestational age at PPROM (22/23 weeks, 24/26 weeks, 27/30 weeks, 31/33 weeks). The first 50 patients will be assigned through simple randomization. For the next step, the marginal totals in each treatment arm for the prognostic factors of the 51st patient will be calculated; the objective is to balance these marginal totals. The 51st patient will be assigned to the arm that improves the balance according to the preselected set of factors between the 2 trial arms. The same process will be applied for each new patient. 10% of randomness will be incorporated into the minimization algorithm, to make the prediction unlikely.

Each woman will receive a unique identification number after inclusion and a treatment box number after randomization.

#### Treatment administration

The allocated treatment box, containing 8 tablets of nifedipine or placebo, will be immediately given to the patient by the local investigator or by his/her delegate, along with a patient compliance form specifying the theoretical timing of each drug intake. The patient will start the protocol as soon as possible with the first intake. Within the first hour after starting nifedipine or placebo, blood pressure, heart rate, and clinical symptoms (such as dyspnea or thoracic pain) will be measured according to each maternity unit’s usual practices. Treatment will continue as long as blood pressure remains within normal limits, with blood pressure and heart rate thereafter measured 2 to 3 times per day. Clinical surveillance and management during the protocol will take place according to local practices, without any additional procedures or data collection. The treatment can be interrupted by the patient and/or the investigator for any reason deemed necessary (including the need for rescue tocolysis).

After each intake, the patient will report its actual date and time on the compliance form, as well as any side effects and comments. After the protocol is completed, the local investigator will collect the treatment box and blister pack and send them to the local pharmacy.

#### Blinding and unblinding procedures

Patients, healthcare providers, pharmacists, and investigators will be blinded throughout the trial. The experimental medication comprises tablets of NIFEDIPINE MYLAN® LP 20 mg - nifedipine. Placebo pink tablets of nifedipine 20 mg will be specifically formulated, manufactured, and packaged (primary packaging: neutral PVC/PVDC/Aluminium blisters) under the responsibility of the Clinical Trials Department (Département Essais Cliniques, DEC) of the General Agency for Health Equipment and Products (Agence Générale des Equipements et Produits de Santé, AGEPS). Nifedipine and placebo will be packed by the Clinical Trials Department in strictly identical numbered sealed boxes, containing one blister pack of 8 tablets of nifedipine 20 mg or placebo.

Unblinding will be requested for any reason considered essential by the investigating doctor by contacting the relevant departments, i.e., the DRCI or the Fernand Widal Hospital poison center (in emergency situations or outside of usual working days and hours).

#### Maternal management and follow-up

Women’s management will otherwise be identical to that in routine practice for PPROM. Usual practices include hospitalization for at least 48 h after the PPROM diagnosis and then hospitalization or home hospitalization until delivery. Except for the experimental intervention, obstetric management (including medical, laboratory, and paraclinical examinations) and treatments (antibiotics, antenatal steroids, and magnesium sulfate) will be based on local protocols and medical teams’ decisions.

Women will be followed up from randomization to discharge home after delivery.

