#### Child follow-up

We will perform a follow-up at 2 years of corrected age, with a self-administered questionnaire sent to the parents, by email and/or postal mail, by using the contact details they provided at inclusion. Besides severe morbidity considered as a secondary endpoint, we will evaluate the children’s growth, health, neurodevelopment, and living conditions (family situation and socioeconomic conditions). Another follow-up evaluation at the age of 5 years is under consideration, if additional funding can be obtained.

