#### Secondary outcome measures

Prolongation of gestation will be evaluated by various different criteria:
Latency duration, defined as the interval from PPROM to delivery.Pregnancy prolongation beyond 48 h after randomization,Pregnancy prolongation beyond 1 week after randomization,Gestational age at delivery,Delivery after 37 weeks of gestation.

Maternal morbidity will be assessed by clinical diagnosis of intrauterine infection, defined as fever (maternal temperature ≥ 38 °C), with no alternative cause identified, associated with at least two of the following criteria: persistent fetal tachycardia > 160 bpm, uterine pain or painful uterine contractions or spontaneous labor, purulent amniotic fluid [21]; and endometritis, based on the association of fever (temperature ≥ 38.0 °C) with uterine tenderness, purulent or foul-smelling lochia, and in the absence of any other cause, during the first 10 days after delivery [59].

For neonatal morbidity, we will isolate each criterion included in the composite primary outcome and assess its association with the intervention. We will also study:
Severe fetal acidemia, defined as cord umbilical artery pH less than 7.00 or base deficit greater than 16 mEq/L (16 mmol/L), or both [60];Respiratory distress syndrome, defined from clinical diagnosis as the presence of clinical signs of respiratory distress (tachypnea, retractions, flaring, grunting, or cyanosis), with a requirement for supplemental oxygen with a fraction of inspired oxygen more than 0.21 and a chest radiograph showing hypoaeration and reticulogranular infiltrates;Mild or moderate BPD, defined as requiring oxygen for at least 28 days plus the need for 21% (mild) - 30% (moderate) oxygen at 56 days postnatal age or 36 weeks’ postmenstrual age or discharge, whichever comes first [53];Grades I-II IVH, defined according to Papile’s classification: subependymal hemorrhage (grade I IVH) or IVH without ventricular dilatation (grade II IVH), diagnosed by ultrasound [54];Late-onset sepsis, diagnosed from positive bacteriology findings in blood or cerebrospinal fluid (confirmed infection) that began after 72 h of life [61].

At 2 years of corrected age, we will evaluate the following criteria [51]:

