### Data collection, management, and monitoring

Maternal adverse events will be recorded prospectively from the first nifedipine or placebo intake to the end of follow-up. Maternal and obstetric data will be available in medical files and will be recorded on the electronic case report form (e-CRF) after the end of the follow-up period. Although this situation is unlikely, if a patient delivers outside the recruiting maternity unit, a duplicate of the medical record will be requested to collect all necessary data.

Neonatal deaths will be reported prospectively. All neonatal data will be recorded on the e-CRF based on medical files, after the infant’s discharge. In NICUs, hospital reports are very precise and state clearly all pathologies and complications diagnosed during the stay. Diagnoses generally use international definitions and are therefore standardized. If any neonate is transferred to a NICU outside of the recruiting center, the investigators will request the hospital report and/or a duplicate of the medical file to collect all necessary data.

This study, including quality controls, will be conducted according to the standard operating procedures of the sponsor, Assistance Publique – Hôpitaux de Paris (AP-HP), the Declaration of Helsinki, and Good Clinical Practices. All data will be recorded by local investigators, research midwives, or trained clinical research technicians on a secure eCRF. Local investigators will be responsible for the accuracy, quality, and relevance of all the data entered. Specific codes will be entered for data missing in the medical records, to distinguish them from data entry errors. Cross-checks for completeness and consistency checks will take place periodically.

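### Endometritis is defined over 10 days after delivery, but planned maternal observation stops at discharge home, so cases arising between discharge and day 10 may be missed

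*Protocol article*

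**What the plan says.** The section Secondary outcome measures gives maternal morbidity two parts. The first is introduced with "Maternal morbidity will be assessed by clinical diagnosis of intrauterine infection". The second is endometritis, a clinical definition based on fever, uterine tenderness and abnormal lochia, counted "in the absence of any other cause, during the first 10 days after delivery".

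The section Maternal management and follow-up fixes the period of observation: "Women will be followed up from randomization to discharge home after delivery". The only hospital stay described there is the antenatal one: "hospitalization for at least 48 h after the PPROM diagnosis and then hospitalization or home hospitalization until delivery". No postpartum length of stay is stated.

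The section Data collection, management, and monitoring says "Maternal adverse events will be recorded prospectively from the first nifedipine or placebo intake to the end of follow-up". On the source of maternal data it says "Maternal and obstetric data will be available in medical files", with entry on the e-CRF once follow-up has ended. Its one provision for obtaining maternal records from elsewhere is that "if a patient delivers outside the recruiting maternity unit, a duplicate of the medical record will be requested".

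After discharge, the only family contact described is the 2-year assessment of the child, made "with a self-administered questionnaire sent to the parents, by email and/or postal mail".

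**The concern.** The outcome window and the observation window end at different times. One closes on day 10 for every woman. The other closes on the day she goes home, which varies between women. Where discharge comes first, the plan defines an event that it has not arranged to see.

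Two things are at stake. First, a rate reported under the stated definition would treat women discharged before day 10 as event-free for days on which nobody was looking, so the absolute rate and the risk difference would be too low. Second, the effective window would depend on length of stay. If stay differed between arms, for instance because mode of delivery did, capture could differ between arms as well.

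This matters because endometritis is half of the planned maternal morbidity assessment. The trial also has no data safety monitoring board and no interim analysis, so the final comparison carries much of the evidence on maternal harm.

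**Working it through.** **1. The windows side by side.** The plan gives no figure on this point to reproduce. The check is a comparison of statements.

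| Item | Ends at | Section |
|---|---|---|
| Endometritis definition | day 10 after delivery | Secondary outcome measures |
| Maternal follow-up | discharge home after delivery | Maternal management and follow-up |
| Maternal adverse event recording | end of follow-up, hence discharge | Data collection, management, and monitoring |
| Infant follow-up | discharge home, or 24 weeks of age if earlier | Neonatal management and follow-up |
| Primary outcome | hospital discharge, or 24 weeks after birth if still in hospital | Primary outcome measure |

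The two infant rows agree. The maternal rows do not agree for any woman discharged before day 10.

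**2. Does anything shown close the gap?**
- The provision for outside maternal records covers delivery elsewhere. It does not cover a postpartum readmission or an outpatient diagnosis.
- The 2-year questionnaire concerns the child.
- The six-monthly extraction under Safety monitoring does not list endometritis.
- No section describes a maternal contact, visit or readmission search between discharge and day 10.

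**3. What incomplete capture would do.** Let *c* be the share of true cases that is observed.

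- Observed rate = *c* × true rate.
- Observed risk difference, equal *c* = *c* × true risk difference.
- Observed RR = (*c* nifedipine / *c* placebo) × true RR, which equals the true RR when the two shares are equal.

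**4. Illustration, equal capture.** From the protocol: 850 women allocated 1:1, so 850 / 2 = 425 per arm, and a two-sided 5% level. Assumed, with no source in the protocol: a true RR of 2, a placebo rate of 2%, 3% or 5%, and *c* of 100%, 75% or 50%. Power uses the normal approximation for two proportions:

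power = Φ{ [ |p1 − p0| √n − 1.96 √(2 p̄ (1 − p̄)) ] / √( p0(1 − p0) + p1(1 − p1) ) }

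For example, with 3% v 6% and full capture: (0.03 × 20.616 − 1.96 × 0.2932) / 0.2924 = 0.15, and Φ(0.15) = 56%.

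| True rates (placebo v nifedipine) | *c* | Observed rates | Risk difference (points) | RR | Power |
|---|---|---|---|---|---|
| 2% v 4% | 100% | 2.0% v 4.0% | 2.0 | 2 | 40% |
| | 75% | 1.5% v 3.0% | 1.5 | 2 | 31% |
| | 50% | 1.0% v 2.0% | 1.0 | 2 | 22% |
| 3% v 6% | 100% | 3.0% v 6.0% | 3.0 | 2 | 56% |
| | 75% | 2.25% v 4.5% | 2.25 | 2 | 44% |
| | 50% | 1.5% v 3.0% | 1.5 | 2 | 31% |
| 5% v 10% | 100% | 5.0% v 10.0% | 5.0 | 2 | 79% |
| | 75% | 3.75% v 7.5% | 3.75 | 2 | 66% |
| | 50% | 2.5% v 5.0% | 2.5 | 2 | 48% |

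**5. Illustration, unequal capture.** With a true RR of 1 (capture shares assumed):
- 50% nifedipine v 70% placebo: 0.50 / 0.70 = 0.71
- 70% v 50%: 0.70 / 0.50 = 1.40
- 50% v 60%: 0.50 / 0.60 = 0.83
- 60% v 50%: 0.60 / 0.50 = 1.20

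The bias can run in either direction.

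**The case against.** The strongest reply has four parts.

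*The 10 days may be a diagnostic limit.* The definition is a cited clinical one, and the limit can be read as the latest onset that counts, with no promise to observe every woman that long. This reading is fair, but it does not remove the mismatch: a case arising after discharge and before the limit still qualifies and is still outside planned observation.

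*The answer may lie in what is not shown.* The schedule of assessments (Table 2) is a missing figure, and the article condenses a full protocol, version 5.0. A later maternal check could appear in either. If it does, the follow-up sentence in the article still needs correcting.

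*Some late cases may be found anyway.* Maternal data come from medical files, so a readmission to the recruiting hospital could be visible. That stands as a possibility, though no search is described and a diagnosis made elsewhere is not covered.

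*The consequence may be small.* Treatment is blinded, RR is a planned effect measure, and equal loss leaves its expected value unchanged. Nothing in the protocol shows that stay or mode of delivery will differ by arm. Power is already below 80% with full capture in every scenario above. All of this stands, and it limits the point to the absolute rates, the risk difference and precision unless capture differs.

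A reader might also infer that a main stated harm of tocolysis is being hidden. The documents do not support that. The maternal harm that the Background reports from the systematic review of earlier trials is chorioamnionitis. Its counterpart here is the intrauterine infection outcome, whose criteria apply before or at delivery and so lie within follow-up.

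**Conclusion.** The two windows conflict as written, and nothing shown reconciles them. Endometritis may therefore be incompletely captured in women discharged before day 10.

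It is tempting to go further and say that the outcome will be under-counted, by half or more. The documents do not support this. They give no postpartum stay, no endometritis rate and no timing of onset, so the share missed cannot be derived, and any loss at all requires that some women go home before day 10. The rates and capture shares in the illustration are assumptions that show direction and scale only. Nor do the documents support a claim that the comparison is biased towards no harm: the RR is biased only if capture differs by arm, and then in either direction.

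The point concerns one secondary safety outcome. It is worth correcting because the correction is cheap and lets the reported harm rate match what was observed.

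**What to change.** Reconcile the outcome definition with the follow-up and adverse event statements in one of two ways.

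1. **Keep the 10-day definition.** For every woman, in both arms alike, add a check of hospital files and readmissions up to day 10 after delivery, record its result on the e-CRF, and carry endometritis recording to the same day. Cost: a small e-CRF change and one record check per woman. A case treated wholly outside hospital could still be missed, and the report should say so.

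2. **Keep follow-up to discharge.** Restate the outcome as endometritis diagnosed before discharge, and report postpartum length of stay by arm so that readers can judge whether the observation windows were comparable. Cost: wording and one descriptive table. Later cases stay unobserved, but the label then matches the data.

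If the full protocol or its assessment schedule already includes a later maternal check, only the follow-up sentence needs amending.
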